## Introduction

1

Lower back pain (LBP) is the leading cause of lost productivity in working age adults due to social and economic hardships of medical rehabilitation.^[1]^ Over 80% of adults report LBP, of which nearly 60% develop severe symptoms that last longer due to poor treatment.^[2]^ Most LBPs are non-specific with no identifiable causes, and conventional treatment often targets only pain relief, leading to poor satisfaction.^[3]^

Korean patients suffering from chronic non-specific lower back pain (cnLBP) prefer traditional Korean medicine (TKM), which utilize multiple personalized and holistic treatment methods. The results of the Korean Medical Use and Consumption Survey conducted in 2017 found cnLBP to be the major reason for visits to Korean medical institutions, with a lifetime healthcare services utilization of 52.7%.^[4]^

*Sogyeonghwalhyeol-tang* (SGHH) finds a mention in the *Wanbinghuichun*, a classical treatise on traditional Chinese medicine, where it is indicated for treatment of abnormal musculoskeletal symptoms such as pain, palsy, and stiffness.^[5]^ It is thought that SGHH functions by rejuvenating blood and dredging the meridians and collaterals.^[6]^ The use of SGHH has been reported in several cases of arthritis-induced pain and neurologic symptoms.^[7–9]^

Chuna manual therapy (CMT) is a therapeutic intervention that stabilizes and maintains orthopedic functions by stimulating the meridian system and correcting displacement of the osteoarticular structure.^[10]^ Randomized controlled trials (RCTs) investigating CMT have demonstrated its efficacy in providing relief from musculoskeletal diseases including cnLBP.^[11]^ Though TKM-based monotherapy is common in RCTs for cnLBP, as it avoids complications arising from interaction effects, the holistic nature of TKM demands multiple interventions. Thus, the integration of multiple modalities such as Chinese *Tuina*, Japanese *Shiatsu*, and American chiropractic and osteopathic medicine, may be considered for cnLBP.

Here, we investigate the efficacy of a combination intervention comprising SGHH and CMT for the treatment of cnLBP. While initially, the trial was based on a 2 × 2 factorial design, an arm consisting of a sham CMT with placebo was considered unethical, due to which the trial will be based on an incomplete factorial design (Table 2).^[12]^

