The primary outcome of this study is to determine the efficacy of a combined multidisciplinary approach using SGHH with CMT on cnLBP, compared to SGHH alone. The secondary outcome is to compare the efficacy of SGHH and a placebo on cnLBP.

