#### Randomization

2.2.2

The flow chart describing the trial protocol is shown in Fig. 1. The study population will enroll 150 eligible participants who will undergo a 7-day run-in period prior to randomization. The participants will be randomly allocated to the SGHH group, SGHH with Chuna group or placebo with Chuna group at a ratio of 1:1:1. Random allocation will be facilitated by a web-based application designed by the contract research organization (CRO), the Institute of Safety and Effectiveness Evaluation for Korean Medicine (ISEE), Kyung Hee University. Independent staff from ISEE will use the SAS 6.1 program for randomization list generation and stratification of the trial sites using block sizes of 3 or 6. Once the participant is randomly assigned to a group, patients will not be informed of the type of allocation that they will receive. However, due to diverse intervention strategies, this trial is designed as an assessor- and analyst-blinded study. Participants will be cautioned on confidentiality of allocation prior to outcome assessment and an independent assessor will evaluate allocation in a secured area without seeking information on treatment allocation that the participant will receive. The final dataset will be sent to data analysts without information on treatment allocations to avoid bias in the analysis of study results. In case of expected abnormal symptoms or occurrence of urgent medical conditions, the site's PI will directly inform ISEE and the sponsor to unblind the treatment allocation according to the standard operating procedures (SOPs).

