#### Sample size

2.5.4

This is a pilot study to explore the efficacy of single or multiple therapies using SGHH and Chuna, feasibility of the study design and effect size for further large-scale studies. A sample size of 150 patients, which is not estimated based on previous studies, was considered after assessing their LBP clinic visit rates, skilled labor availability, budget, and expected attrition at each site.

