**Table 4 T4:**

Study hypotheses for statistical analysis plan.

Baseline demographic data will be analysed using a *t* test for continuous data and a chi-square test for categorical data. All outcome measures will be calculated as the mean changes between pre- and post-treatments that will be compared using a paired *t* test for intragroup analysis and a Student *t* test for intergroup analysis. Any variables that are to be assessed repeatedly during the trial will be analysed by comparing the mean changes over time using a repeated-measures ANOVA test. Missing data will be using the Last-observation-carried-forward (LOCF) analysis method. There will be no interim analysis for any reason. And we will not establish the data and safety monitoring committee due to the resource and personnel limitations.

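### Intragroup paired t tests are planned for every outcome without being labelled descriptive, although a within-arm change cannot show a treatment effect

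*Protocol article*

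**What the plan says.** Section 2.5.5 (Statistical management, text beneath Table 4) sets the analysis for every outcome in one sentence: "All outcome measures will be calculated as the mean changes between pre- and post-treatments that will be compared using a paired" t test for change within each group. The same sentence adds a Student t test for differences between groups, and the next adds a repeated-measures ANOVA: "test for intergroup analysis. Any variables that are to be assessed repeatedly during the trial will be analysed by comparing the mean changes over time". The visible text neither ranks these tests nor calls the within-group test descriptive. Table 4, which is said to summarise the strategy for each hypothesis, is not shown.

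The objectives in the Introduction are comparative. The primary one concerns the "efficacy of a combined multidisciplinary approach using SGHH with CMT on cnLBP, compared to SGHH alone". For the other, "The secondary outcome is to compare the efficacy of SGHH and a placebo on cnLBP". Section 2.5.1 likewise says that changes in pain will be analysed between the three groups.

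On design, the Introduction explains that "an arm consisting of a sham CMT with placebo was considered unethical, due to which the trial will be based on an incomplete factorial design". Section 2.2.2 has patients "randomly allocated to the SGHH group, SGHH with Chuna group or placebo with Chuna group at a ratio of 1:1:1". All three arms therefore contain SGHH, Chuna manual therapy (CMT), or both.

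**The concern.** Pain scores in a chronic pain trial can fall over four weeks for reasons unrelated to treatment: natural fluctuation, regression to the mean, and response to attention or placebo. A paired t test asks only whether the mean change in one arm is zero. Any of these causes can make it significant. Nor does significance in one arm and not in another test a difference between them.

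The design adds a reason for care. Section 2.5.4 gives as one aim the exploration of efficacy for the therapies used singly as well as together, and the Discussion speaks of evaluating herbal monotherapy. No arm shows what happens without active treatment. A reader who wants a verdict on SGHH alone will find one p-value that seems to give it, the paired test in the SGHH arm, and that p-value cannot support the claim.

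**Working it through.** **Inputs from the protocol article.** Total sample 150 (section 2.5.4: "A sample size of 150 patients, which is not estimated based on previous studies"); three arms at 1:1:1 (section 2.2.2), so 150/3 = 50 per arm. The article gives no significance level, SD or expected change, so it has no power figure to reproduce.

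**Assumptions.** Two-sided α = 0.05; SD of NRS change s = 1.5, 2.0 or 2.5; background improvement m = 0.5, 1.0 or 1.5 points, the same in every arm; no treatment effect; normally distributed changes.

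**Step 1: within-arm paired t test.** The statistic follows a noncentral t with n − 1 = 49 degrees of freedom and noncentrality λ = (m/s)·√n, where √50 = 7.071. For m = 1.0 and s = 2.0, λ = 0.5 × 7.071 = 3.54, and the rejection probability is 0.934. The full grid at n = 50 is:

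| SD of change | m = 0.5 | m = 1.0 | m = 1.5 |
|---|---|---|---|
| 1.5 | 0.637 | 0.996 | 1.000 |
| 2.0 | 0.410 | 0.934 | 0.999 |
| 2.5 | 0.284 | 0.792 | 0.986 |

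The range is therefore 28% to 100%. With 40 per arm and SD 2.0, to allow for dropout, the row becomes 0.338, 0.869 and 0.996.

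**Step 2: between-arm Student t test.** If both arms improve by the same m, the expected difference is m − m = 0, and the test should reject at its nominal rate. In 20,000 simulated trials per setting at n = 50, it rejected in 0.048 to 0.052 across the whole grid.

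**Step 3: comparing p-values across arms.** For two identical, independent arms with within-arm rejection probability p, the chance that exactly one is significant is 2p(1 − p). At s = 2.0 and m = 0.5 this is 2 × 0.410 × 0.590 = 0.48 (simulated 0.486). At m = 1.0 it is 2 × 0.934 × 0.066 = 0.12 (simulated 0.124).

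**Step 4: what the randomised arms can compare.**

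- SGHH + CMT versus SGHH: the effect of adding CMT to SGHH.
- SGHH + CMT versus placebo + CMT: the effect of adding SGHH to CMT.
- SGHH versus placebo + CMT: the arms differ in both components, so neither is isolated.

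The second is a randomised, placebo-controlled contrast for SGHH on a common CMT background. None compares SGHH alone with no active treatment.

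**The case against.** The strongest reply is that the plan already does the right thing. The sentence that plans the paired test also plans the between-group test, both objectives are between-arm, and section 2.5.1 describes the primary outcome in those terms. That the paired test is named first sets no priority. All of this stands, and it limits the point to the status of the within-group tests.

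Three stronger readings are tempting, and the article does not support them.

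- A reader might infer that the trial will declare efficacy from within-arm p-values. No visible text says so, and Table 4 cannot be checked.
- A reader might infer that dropping the placebo plus sham arm causes the flaw. It does not: a paired test inside the SGHH arm would be just as uninformative with a fourth arm present. The missing arm only removes the comparison that a reader may then seek elsewhere. The article discloses the omission, and its Discussion partly acknowledges the design's limits.
- A reader might infer that SGHH has no randomised contrast at all. It has one, on a CMT background.

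Two further cautions are fair. The eligibility table is not shown, so a pain threshold at entry, and with it the strength of regression to the mean, is unknown; natural course and placebo response carry the argument without it. The background improvement is also assumed: at 0.5 points with SD 2.0 to 2.5 the paired test rejects in 28% to 41% of trials, not nearly always. Even so, that is far above 5%.

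**Conclusion.** The point holds in a limited form. Section 2.5.5 fixes an inferential within-arm test for every outcome without saying what it may be used for. Under the stated assumptions that test is significant in about 28% to 100% of trials of an ineffective treatment, against about 5% for the between-arm test that is also planned. The exact percentages depend on the assumed improvement and SD; the contrast between the two tests depends only on some background improvement being shared across arms. What is shown is an open route to misreading, chiefly for SGHH as monotherapy, and not a declared intention to take it. For a self-described pilot with comparative objectives, the severity is minor.

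**What to change.** In section 2.5.5, replace the intragroup paired t tests with within-arm mean changes and 95% confidence intervals, presented as description only. Add that efficacy conclusions rest on the randomised between-group differences, and that the randomised contrast for SGHH is SGHH + Chuna versus placebo + Chuna. If Table 4 lists within-group hypotheses, bring it into line.

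The cost is a sentence or two of text and fewer p-values in the report. The within-arm means and intervals keep the descriptive information on change that is useful for planning the larger trial.

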#### Primary outcome measurement

2.5.1

We will use numeric rating scale (NRS)^[17]^ as the primary outcome for assessing the severity of LBP, by evaluating intensity of low back pain (LBP) on a scale range of 0 (no pain at all) to 10 (worst pain imaginable). The participants will be asked to rate their pain on a defined scale at each assessment. The changes in the pain intensity between the 3 groups will be analyzed.

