#### Statistical management

2.5.5

An independent statistician from ISEE who is blinded to the treatment allocation will conduct data analysis by both intent-to-treat (ITT) and per-protocol (PP) analysis. The data analysis strategy for testing each study hypotheses is summarized in Table 4.

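### The repeated-measures ANOVA does not by itself isolate or estimate the primary contrast of SGHH with CMT versus SGHH; a baseline-adjusted mixed model would, at no extra data cost

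*Protocol article*

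**What the plan says.** All references are to the protocol article.

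- **Objective (end of the Introduction).** The primary question is the "efficacy of a combined multidisciplinary approach using SGHH with CMT on cnLBP, compared to SGHH alone". The secondary question compares SGHH with placebo.
- **Primary outcome (2.5.1).** The outcome is the 0–10 pain NRS, rated at every assessment. The section adds: "The changes in the pain intensity between the 3 groups will be analyzed".
- **Analysis (2.5.5).** Two methods are named. First, "All outcome measures will be calculated as the mean changes between pre- and post-treatments", with a paired t test within groups and a Student t "test for intergroup analysis". Second, repeatedly assessed variables are to be "analysed by comparing the mean changes over time using a repeated-measures ANOVA test".
- **Link from hypotheses to tests (2.5.5).** "The data analysis strategy for testing each study hypotheses is summarized in Table 4". The body of that table is not in the text available for review.
- **Design (2.2.2 and 2.5.4).** There are 150 participants, allocated "at a ratio of 1:1:1" to three arms, with visits every two weeks over four weeks of treatment and four of follow-up. The number comes from feasibility. One stated purpose is to learn the effect size for later large trials.

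**The concern.** The NRS is rated at each assessment, so it falls under the ANOVA sentence as well as the t-test sentence. The ANOVA is therefore a named analysis of the primary outcome.

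The sentence on the ANOVA describes a comparison over time. Read literally, that is the time term, which becomes significant when all arms improve together. Read with the three-group sentence in 2.5.1, it is an omnibus group-by-time test, which any arm or visit can trigger. Either way, a significant F cannot be credited to adding CMT. It also supplies no difference with a confidence interval, which a pilot needs to plan its successor.

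A second, conditional issue is that a classical repeated-measures F test on within-subject terms relies on sphericity. Scores from neighbouring visits are often more alike than scores from distant ones, and an uncorrected test then rejects somewhat too often.

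**Working it through.** The plan states no power, effect size or SD, so it has no figure to reproduce.

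**Inputs from the protocol.** 150 participants at 1:1:1 gives 150/3 = 50 per arm. Visits are two-weekly over 4 + 4 weeks, and treatment ends at week 4.

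**Assumptions.** Two-sided 5% level. Five assessments (weeks 0, 2, 4, 6, 8), or three if only the treatment period counts. SD of 1 at each visit, and an SGHH with CMT minus SGHH effect of 0.5 SD at week 4. The main case takes AR(1) correlation of 0.6 between neighbouring visits, so the baseline to week-4 correlation is r = 0.6² = 0.36.

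**1. What the F test tests.** With three arms and five visits, group-by-time has (3 − 1) × (5 − 1) = 8 degrees of freedom. The primary contrast at one visit has 1. In a simulation where all three arms improved equally by 0.5 SD, the time term was significant in 100% of trials although the arms did not differ.

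**2. Planned t test against a baseline-adjusted contrast at week 4.** With 50 per arm the noncentrality is d × √(50/2) = 5d.

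- Change score: SD = √(2(1 − r)) = √1.28 = 1.131; d = 0.5/1.131 = 0.442; noncentrality 2.21; power 59%.
- Baseline-adjusted: SD = √(1 − r²) = √0.8704 = 0.933; d = 0.5/0.933 = 0.536; noncentrality 2.68; power 76%.

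Simulation of the same setting gave 58% and 76%. The variance ratio of adjusted to change score is (1 − r²)/(2(1 − r)) = (1 + r)/2, here 0.68. The gain depends on r:

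| r (baseline to week 4) | variance ratio | change t test | baseline-adjusted |
|---|---|---|---|
| 0.20 | 0.60 | 50% | 71% |
| 0.36 | 0.68 | 59% | 76% |
| 0.50 | 0.75 | 70% | 82% |
| 0.70 | 0.85 | 89% | 93% |

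**3. Omnibus power.** The effect was 0.5 SD at week 4, fading to 0.25 SD by week 8, and half as large in placebo with CMT, at neighbouring-visit correlation 0.6. The uncorrected three-arm group-by-time test had about 33–35% power. Varying the assumed effects at weeks 2 and 6 moved this between about 31% and 43%.

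**4. Null rejection of the group-by-time test.** Simulation with 10,000 trials per setting, 50 per arm, two or three arms:

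| Setting | Uncorrected | Greenhouse-Geisser |
|---|---|---|
| 5 visits, AR(1) 0.5 to 0.9 | 6.3–8.9% | 4.7–5.4% |
| 3 visits, AR(1) 0.5 to 0.9 | 5.4–6.2% | 4.5–5.3% |
| 3 or 5 visits, compound symmetry 0.5 | 4.8–5.4% | 4.5–5.2% |

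The between-group main effect needs no sphericity and stayed at 4.5–5.5% throughout.

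**The case against.** The strongest reply is that the primary contrast already has a test. The sentence before the ANOVA sentence gives a two-sample t test on pre-to-post change for every outcome. It compares SGHH with CMT against SGHH directly, and sphericity does not enter. Table 4 is said to set out the strategy for each hypothesis; its body is not shown, and it may state which arms enter which test. This stands. A reader might infer that the plan never tests its primary contrast, and the document does not support that.

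A reader might also infer that the ANOVA rejects too often. That is not supported either. The article does not say that F tests go uncorrected or that all three arms enter one ANOVA. The three-group sentence in 2.5.1 describes the outcome and is compatible with pairwise tests. A sphericity correction is a detail that a journal article may leave to the analysis plan. The inflation is therefore conditional, and absent or small in several plausible settings.

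It is fair to add that setting 33–35% against 76% would exaggerate the gain, because the plan's own t test reaches about 58%. That smaller gap comes from baseline adjustment. The trial is also a pilot, with no confirmatory claim tied to this F test.

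What remains is that the NRS is subject to both methods, the visible text ranks neither, and the named longitudinal method neither isolates nor estimates the contrast of interest.

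**Conclusion.** The point holds in a limited form. The repeated-measures ANOVA, as worded, is a time-effect or omnibus test and does not by itself isolate or size the primary contrast. The t test can do so, but less efficiently: about 58% power against 76% with baseline adjustment, given a 0.5 SD effect, 50 per arm with complete data, and a baseline to week-4 correlation of 0.36. The gap narrows as that correlation rises, to 89% against 93% at 0.70.

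Excess rejection of about 6–9% applies only to an uncorrected group-by-time test with five serially correlated visits. With three visits it is at most about 6%. All correlations, the effect profile and the visit count are assumptions, since the document gives no SD or effect size. This is a free improvement in method, not an error that invalidates the planned analysis.

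**What to change.** Replace the repeated-measures ANOVA in 2.5.5 by a mixed model for repeated measures, with arm, visit, arm-by-visit, baseline and baseline-by-visit as fixed effects and an unstructured covariance across visits. From this one model report, with 95% confidence intervals at the end of treatment:

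- SGHH with CMT minus SGHH, for the primary question;
- SGHH with CMT minus placebo with CMT, for the secondary question.

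The unstructured covariance removes the sphericity question, and the estimates serve the planning of the later trial. If the ANOVA is kept as support, state that the group-by-time term is the one read, not the time term, and apply a Greenhouse-Geisser correction.

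The cost is a change of wording and one standard model call. No new data, visits or participants are needed.

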**Figure 1 F1:**
[figure not shown]
Study flow diagram.

After randomization, the participants will receive medication for 4 weeks, and an additional 4 weeks of follow-up, during which they will visit the clinic once every 2 weeks. To manage adherence to the interventional products, study staff will ask participants to return the unused products for calculating compliance at every visit.

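### LOCF is the only stated way of handling missing pain scores, and it can bias the between-arm NRS contrast in either direction when dropout or time course differs by arm

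*Protocol article*

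**What the plan says.** Section 2.5.5 (Statistical management, text after the Table 4 caption) states: "Missing data will be using the Last-observation-carried-forward (LOCF) analysis method". No other missing-data method and no sensitivity analysis is named.

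The same paragraph sets the analyses that the filled data enter. "All outcome measures will be calculated as the mean changes between pre- and post-treatments", to be compared by paired and Student t tests; variables measured repeatedly "will be analysed by comparing the mean changes over time using a repeated-measures ANOVA test".

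Section 2.5.1 makes the NRS the primary outcome: "The participants will be asked to rate their pain on a defined scale at each assessment", and "The changes in the pain intensity between the 3 groups will be analyzed". The text after Figure 1 describes 4 weeks of medication and then "an additional 4 weeks of follow-up, during which they will visit the clinic once every 2 weeks".

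The article expects missing data. Section 2.5.4 counts attrition among the considerations behind the sample of 150. Section 2.4 allows the investigator to end participation for use of barred medicines or poor adherence.

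**The concern.** LOCF is a sound guess only if a participant's pain would have stayed still after the last visit. That is hard to assume across a treatment phase and then an off-treatment phase. Someone lost straight after baseline is scored as having no change. Someone lost after week 2 keeps the week-2 score. Someone lost after week 4 carries an on-treatment score into follow-up. How many participants fall into each class, and what each class carries, can differ by arm, and that difference goes straight into the contrast. The filled rows are also flat over time, which changes the within-person pattern that the repeated-measures ANOVA tests.

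Unequal dropout is plausible here. The main comparison in the Introduction is herbal medicine plus manual therapy against herbal medicine alone, so the visit burden differs visibly, and section 2.2.2 claims blinding of assessors and analysts only.

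What is at stake is the estimate itself. Section 2.5.4 says that the pilot is to explore an effect size for larger studies, and the Discussion adds power for their sample-size calculation.

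**Working it through.** The article gives no SD, alpha, power, effect size or dropout rate, so there is no stated figure to reproduce. What follows is an illustration.

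**From the article:** 150 participants at 1:1:1, so 150 / 3 = 50 per arm; NRS 0-10; 4 weeks of treatment and 4 weeks of follow-up.

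**Assumed:** NRS at weeks 0, 2, 4, 6 and 8 (inferred from the 2-weekly visits and rating at each assessment); SD 2; correlation 0.6 between visits; dropout unrelated to outcome; half of the on-treatment dropouts last seen at baseline and half at week 2; Student t test on the LOCF change, two-sided 5%.

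**1. Week 4, no true difference.** Let an arm's mean NRS be m0, m2, m4 and its dropout share d. The LOCF mean at week 4 exceeds the true mean by

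d × [½(m0 − m4) + ½(m2 − m4)].

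- Profile 6/5/4: d × (½ × 2 + ½ × 1) = 1.5d.
- Profile 6/5.5/5: d × (½ × 1 + ½ × 0.5) = 0.75d.

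The bias in the contrast is this factor times the dropout gap. Rejection rates are simulated and vary by about one percentage point between runs.

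| Dropout | Gap | Bias, 6/5.5/5 | Bias, 6/5/4 | Type I error |
|---|---|---|---|---|
| 20% v 20% | 0 | 0 | 0 | about 5% |
| 10% v 20% | 0.10 | 0.075 | 0.15 | 5-7% |
| 5% v 20% | 0.15 | 0.11 | 0.225 | 7-9% |
| 5% v 30% | 0.25 | 0.19 | 0.375 | 9-19% |

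With equal dropout the error rate stays nominal, so the inflation in this t test comes from the shifted mean.

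**2. Week 4, true difference −1.0.** Better arm 6/4.5/3, other arm 6/5/4.

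- 20% in each arm: better arm 0.8 × (−3) + 0.1 × (−1.5) = −2.55; other arm 0.8 × (−2) + 0.1 × (−1) = −1.70; difference −0.85.
- 30% in the better arm, 10% in the other: −2.325 − (−1.85) = −0.475.
- 10% in the better arm, 30% in the other: −2.775 − (−1.55) = −1.225.

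The bias can shrink or enlarge the effect. Equal dropout does not remove it when the time courses differ.

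**3. Follow-up.** Assume 6/5/4/4.5/5 in both arms, so the true week-8 mean is 5.0.

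- Lost during treatment: the carried score averages (6 + 5) / 2 = 5.5, which is 0.5 too high and hides benefit.
- Lost after week 4: the carried score is 4.0, which is 1.0 too low and suggests lasting benefit.

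A 10% v 30% loss after week 4 therefore creates a false week-8 difference of 1.0 × 0.20 = 0.20 (rejection about 9%). The same gap during treatment creates 0.5 × 0.20 = 0.10 in the opposite direction. If the arms agree at week 4 but truly differ by 2.0 at week 8, equal loss of 20% after week 4 shrinks that to 1.6.

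**The case against.** The strongest reply is that nothing in the article shows the harm will occur. It states no dropout rate, and a chronic-pain population after a 7-day run-in may show only a small fall. With small gaps or a shallow fall, the bias is 0.07-0.15 points and the error rate stays at 5-7%. The trial also calls itself a pilot and its results preliminary, so type I error is a weak ground for alarm. These points stand. They limit the severity and require conditional wording. They do not make LOCF a good main rule, because neither the gap nor the time courses are known when the method is fixed.

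Three stronger readings are tempting, and the document supports none of them.

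- A reader might infer that the primary contrast is biased. It can be; with equal dropout and identical profiles it is not.
- A reader might infer that the arm losing more participants looks worse whatever its treatment does. That needs falling pain and dropout unrelated to outcome.
- A reader might infer that follow-up is biased toward lasting benefit. That holds for those lost after week 4; those lost earlier pull the other way.

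The reach also has limits. The content of Table 4, which links hypotheses to analyses, cannot be read here. If post-treatment means week 4, the follow-up distortion touches the repeated-measures ANOVA and any week 6 or 8 comparison, but not the pre/post t test. Running both ITT and per-protocol analyses is no answer, since a per-protocol set does not test the missing-data assumption.

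**Conclusion.** The point holds in conditional form. The article commits to LOCF as its one missing-data method, so this is a stated choice and not detail left to an unseen analysis plan. Under the assumptions above and no true difference, the distortion at week 4 runs from nil to about 0.38 NRS points, and type I error from about 5% to 19%. The upper end needs a 25-point dropout gap and a 2-point fall. The direction cannot be predicted in advance. The effect on the repeated-measures ANOVA was reasoned and not quantified. A reader might take the upper figures as grounds to call this a must-fix. For a self-declared pilot with assumed inputs they do not carry that weight. It should be fixed, because the effect estimate is the pilot's main product.

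**What to change.** In section 2.5.5, replace LOCF and the repeated-measures ANOVA as the main analysis with wording such as: *NRS will be analysed with a mixed model for repeated measures on all observed post-baseline values, with arm, visit, arm-by-visit interaction, baseline NRS and site, without imputation. The between-arm contrast will be estimated at the end-of-treatment visit. A multiple-imputation analysis with delta adjustment, over a range set before unblinding, will examine departures from missing at random.* LOCF may remain as a secondary sensitivity analysis, labelled as such. Use the same model for RMDQ and EQ-5D where they are measured repeatedly.

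The cost is a change of wording, standard software and a little more analysis work, with no new data or visits. The downside is that the main model relies on missing at random, which the delta-adjusted analysis is there to probe.
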